### 2.9. Withdrawal of Participants

In accordance with the Declaration of Helsinki [55], all participants have the right to withdraw from the study at any time, without the need to provide a reason, and without affecting their future medical care. Participants will be informed of this right prior to giving consent. If a participant decides to withdraw, it will be clarified that they are only discontinuing the study treatment while continuing follow-up visits. Should a participant wish to fully withdraw from the study, their decision will be respected. Efforts will be made to determine the reason for withdrawal, although participants are not required to provide any explanation. Data already collected will be retained and included in the final analysis. The PI may also withdraw participants for various reasons, including but not limited to protocol violations, intercurrent illness, adverse events, serious adverse events, suspected unexpected serious adverse reactions, administrative reasons, or if participation in the trial interferes with ongoing care or results in symptomatic worsening.

In these cases, participants will continue to be followed up with the same schedule of research assessments as those who remain in the study, until they complete the 12-week follow-up period or until they develop frank psychosis, whichever occurs first. Participants who experience progression to first-episode psychosis will exit the study intervention, be classified as treatment failure, and only be assessed for safety outcomes until completing the 12-week follow-up period.

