## 2. Materials and Methods

### 2.1. Trial Design

This is a 12-week, open-label, investigator-initiated, proof-of-concept, single-arm study (Phase-2 Pilot Study) assessing the effect of um-PEA 600 mg/day in CHR individuals presenting with APS [1]. Within the first 12 months from the first participant recruitment, we will assess the feasibility of enrolling a minimum of 20 CHR participants and whether at least 80% of participants have completed the 12-week follow-up. After completing the initial 12-week phase, participants will be proposed to enter a 24-week extension phase of the study to evaluate the clinical stability of the treatment. Based on clinical judgement of the improvement obtained at that point, um-PEA might be titrated to 1200 mg/day. Each participant will undergo um-PEA treatment for a maximum of 36 weeks (Table 1). Our purpose is to examine: (i) um-PEA ability to alleviate APS and anxiety symptoms in CHR patients; (ii) um-PEA safety and tolerability; (iii) the biological basis of um-PEA effect. The study was approved by the Department of Medicine (DMED) at University of Udine (Institutional Review Board: 93/2023) in June 2023 (https://osf.io/wn2kf, accessed on 5 December 2024).

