#### 2.3.2. Research Endpoints

We will primarily address whether um-PEA added to treatment as usual (TAU) in CHR patients improves APS. Our secondary research questions are whether um-PEA added to TAU in CHR patients improves APS to the extent that patients no longer satisfy the diagnostic criteria for the CHR state, relieves APS-associated distress, improves CHR-related anxiety symptoms, and ameliorates social and role functioning, as well as general psychopathology and wellbeing measures. Therefore, our primary endpoint will be the assessment of APS severity as measured using the CAARMS [1]. As per the secondary endpoints: (i) APS-associated distress will be measured using the CAARMS [1]; (ii) severity of CHR-related anxiety symptoms will be measured using the Hospital Anxiety and Depression Scale (HADS) [43]; (iii) the level of impaired global functioning will be measured using the Social and Role functioning Scale [44]; (iv) clinical remission, defined as no longer meeting the APS criteria [1] will be measured using the CAARMS [1]; (v) general psychopathology and wellbeing changes will be measured using the CAARMS [1].

All the study endpoints for the 12-week clinical trial will be assessed by comparing follow-up (FUP) visits and baseline. For those participants continuing in the 24-week extension phase, change (FUP visit minus baseline) in the severity of psychotic symptoms as measured using the CAARMS will be compared with the group of those willing to discontinue um-PEA and continue with TAU. Should the psychopathological condition require TAU adjustments based on clinical judgement, this will be mentioned in a specific section of the trial case report form (CRF; https://osf.io/2vayh, accessed on 5 December 2024).

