### 2.6. Intervention

Participants will initially undertake a 12-week daily treatment with oral um-PEA 600 mg in tablet form (Normast^®^). During the 24-week extension phase of the study, the trial medication will be taken from once a day up to twice a day (600–1200 mg per day), based on clinical judgment of the improvement obtained at that point, around mealtime. Being a food supplement/nutraceutical, um-PEA can be purchased at pharmacies without a medical prescription [52]. While unknown risks cannot be excluded, serious adverse events including overdose have not been documented [53,54]. Um-PEA will be obtained by a pharmaceutical company operating under good manufacturing practice conditions with appropriate certification.

The information presented on the labels for um-PEA will comply with applicable national and local regulations. Only qualified physicians clearly given this role by the PI will prescribe the study medication on the study delegation log. Only people designated by the PI will collect medication. Only um-PEA supplied for this study will be dispensed against the study specific prescription. Full accountability records will be completed including recording the batch, expiry date, people dispensing/checking the prescription, quantity and date of drug returns, empty packaging. Nothing will be destroyed without the authorization from the PI.

Um-PEA will be stored at room temperature (<25 °C) and not kept in a refrigerator, in compliance with local regulations. It will be stored in a secure area away from other treatments and clearly marked for this study.

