#### 2.8.2. Missing Data

We expect withdrawn patients to be missing at random, and very few participants withdrawing consent. All patients having at least one post-baseline outcome measure will be included in each analysis. Nonetheless, patterns of missing data will be explored to investigate any evidence against missing at random, whose impact on the analysis will be considered by introducing imputation methods (i.e., Multiple Imputation or MissForest approach, depending on the missing data type).

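### The follow-up rule after withdrawal by the investigator or conversion to psychosis stops at week 12, while treatment and scheduled visits run to week 36

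*Protocol article*

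**What the plan says.** Section 2.9 lists reasons for which the PI may withdraw a participant. They include adverse events and serious adverse events, "or if participation in the trial interferes with ongoing care or results in symptomatic worsening". It then gives the follow-up rule: "In these cases, participants will continue to be followed up with the same schedule of research assessments as those who remain in the study", with the end point "until they complete the 12-week follow-up period or until they develop frank psychosis, whichever occurs first". Participants who convert to first-episode psychosis leave the intervention, are counted as treatment failures, and will "only be assessed for safety outcomes until completing the 12-week follow-up period".

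The rest of the article describes a longer study:

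- Section 2.1: "Each participant will undergo um-PEA treatment for a maximum of 36 weeks".
- Section 2.6: "During the 24-week extension phase of the study, the trial medication will be taken from once a day up to twice a day", which means 600 to 1200 mg/day. The first 12 weeks are at 600 mg/day only.
- Section 2.3.2: for those who continue into the extension, the change in CAARMS severity "will be compared with the group of those willing to discontinue um-PEA and continue with TAU".
- Section 2.3.3: the incidence of adverse effects is measured with the UKU scale over the study period.
- Table 1: CAARMS and UKU at T3 (week 24) and T4 (week 36). Physical examination, ECG, urinalysis and blood tests are done at T2 and T4 but not at T3.
- Section 2.8.2: "All patients having at least one post-baseline outcome measure will be included in each analysis". Missing-data patterns will be explored and imputation is foreseen.

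**The concern.** The two end dates in Section 2.9 are not expressly tied to exits in the first phase, and the article gives no other rule for a PI withdrawal or a conversion after week 12. Someone who leaves in either way during the extension has already completed the 12-week follow-up, so the rule asks for nothing more.

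Two things are at stake. The first is safety information. The course and resolution of an adverse event that led to withdrawal, or the safety of a person who has just converted, need not be assessed, including after exposure to 1200 mg/day. The second is the extension comparison in Section 2.3.2. A continuer withdrawn because of worsening contributes no later CAARMS. If the exit falls between T2 and T3, the last scheduled score is the one at T2, before the worsening.

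The rule is also uneven. For a participant who chooses to stop treatment, Section 2.9 foresees continued follow-up visits and states no week limit. A participant whom the PI removes for a serious adverse event has the week-12 limit.

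**Working it through.** **Timeline (Sections 2.1 and 2.9, Table 1).** The stated maximum treatment duration is reproduced: 12 + 24 = 36 weeks, with T4 at week 36. The rule in Section 2.9 covers 12 of the 36 weeks. The other 36 − 12 = 24 weeks (24/36 = 67%) contain T3, T4 and all exposure above 600 mg/day.

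**What an exit after T2 removes (Table 1).**

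| Exit | CAARMS no longer required | UKU no longer required | Other checks no longer required |
|---|---|---|---|
| Between T2 and T3 | T3, T4 | T3, T4 | T4 physical examination, ECG, urinalysis, blood tests |
| Between T3 and T4 | T4 | T4 | the same T4 set |

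For converters, CAARMS ends at conversion in any case, because they are assessed for safety only. For them the loss is UKU and the T4 checks.

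**Age of the last scheduled assessment at exit.**

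- UKU: T2 to T3, or T3 to T4, is 12 weeks. With the ±14-day windows, T2 at week 10 and T3 at week 26 give 26 − 10 = 16 weeks.
- ECG and blood tests: T2 to T4 is 36 − 12 = 24 weeks. With T2 at week 10 and treatment capped at week 36, an on-treatment exit gives at most 36 − 10 = 26 weeks. These intervals follow from Table 1 and apply to every continuer. Section 2.9 adds only that nothing is required afterwards.

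**Expected conversions in the extension.** Inputs: two-year risk p = 16–19% (Introduction), 104 weeks in two years, and either all 20 entering or 20 × (1 − 0.20) = 16 entering (the 20% drop-out bound in Section 2.2). Assumption: constant hazard.

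Risk over 24 weeks = 1 − (1 − p)^(24/104)

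- p = 0.16: 0.0394
- p = 0.19: 0.0475

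| Entrants | p = 0.16 | p = 0.19 |
|---|---|---|
| 16: expected conversions | 0.63 | 0.76 |
| 20: expected conversions | 0.79 | 0.95 |
| 16: chance of at least one | 0.475 | 0.541 |
| 20: chance of at least one | 0.553 | 0.622 |

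About half of these fall before T3 (0.32 to 0.48) and half after it (0.31 to 0.47).

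**PI withdrawals.** The article gives no rate. If 5–20% of entrants were withdrawn (assumption only), that would be 0.05 × 16 = 0.8 to 0.20 × 16 = 3.2 people, or 0.05 × 20 = 1 to 0.20 × 20 = 4.

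**The case against.** The strongest reply is that the 12-week follow-up is the article's name for the first phase. Sections 2.1 and 2.3.1 use it so, and entry to the extension is optional. On that reading Section 2.9 tells staff to keep early leavers under observation until the first phase ends, and it does not forbid anything later. The article condenses a fuller protocol that may hold the extension rule. This reading is plausible, and it rules out saying that the plan prohibits later assessment. It does not close the gap. The article states a rule with an end date, twice, and no rule in it covers these exits after week 12. Either reading calls for the same clarification.

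Several stronger inferences are tempting, and the document does not support them:

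- *That the safety endpoint is lost.* Section 2.3.3 concerns incidence. An event that prompts withdrawal is known at exit, and Section 2.8.1 reports adverse-effect rates and reasons for drop-out. What is lost is follow-up after exit, in people who have stopped treatment. The Discussion also cites earlier safety experience at 300–1200 mg/day.
- *That conversions bias the extension comparison in one direction.* Conversion ends CAARMS in continuers and discontinuers alike. Treatment-failure coding has no week limit and is not at issue.
- *That the extension comparison would be sound but for this.* It compares self-selected, open-label groups, so a few missing late scores are minor beside that confounding. Section 2.8.2 keeps earlier scores and plans missing-data checks. This reduces the loss, though imputation cannot show what happened after a worsening as well as an observed score can.
- *That ECG and blood tests could be 28 weeks old at such an exit.* Adding both visit windows gives 28, but the 36-week treatment cap limits an on-treatment exit to 26.

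**Conclusion.** The point holds as a gap confined to the extension. Section 2.9 ends research assessment after PI withdrawal, and safety assessment after conversion, at week 12, and nothing in the article covers the same exits between weeks 12 and 36.

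The size is small. Fewer than one extension conversion is expected, given the article's two-year risk, a constant hazard and 16 to 20 entrants. The number of PI withdrawals cannot be derived from the document, and the range of about 1 to 4 people rests on an assumed rate. The Baseline/T1/T2 primary analysis, the feasibility endpoints and the sample size do not change. In a 20-person pilot that lists tolerability among its aims, the few people affected are still those whose later safety data are of most interest, and the visits that would supply them are already scheduled. This is a cheap improvement of low severity.

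**What to change.** In both sentences of Section 2.9, replace the 12-week limit with: *until week 12 for exits before T2, or until week 36 (T4) for participants who entered the extension and exit after T2*. Keep the existing rules that research assessments stop at frank psychosis and that converters are assessed for safety only. PI-withdrawn continuers then keep CAARMS and UKU at the remaining visits plus the T4 checks. Converters keep UKU and the T4 safety checks.

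The limit should depend on the time of exit and not on having completed T2. Someone withdrawn at week 6 stays on the common schedule and so completes T2, and should not be carried to week 36.

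Because converters' later CAARMS would still not be collected, add one sentence to Section 2.3.2: report extension conversions in continuers and in discontinuers beside the CAARMS comparison.

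The cost is these wording changes and at most two already scheduled visits (T3 and T4) for each of the few people concerned.

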## 3. Discussion

Despite substantial advancements in early detection and prognosis, current research still converges towards the lack of effective interventions for transition to psychosis, subtle psychotic symptoms, functional status, and depression, among CHR individuals [3,5,56]. Noteworthy, APS, negative symptoms, and impairment in social and role functioning affect the quality of life of CHR individuals similarly to those of psychosis patients [57]. The present proof-of-concept Phase-2 study proposes the use of a nutraceutical, the fatty acid amide PEA in its ultramicronized form, to treat APS and reduce psychic distress in CHR individuals. In parallel, um-PEA modulation of potential CHR state biomarkers across the inflammatory, endocannabinoid, and microbiome systems will be assessed.

This study protocol should be seen considering some strengths and limitations. First, our study provides a reasonably extended treatment for help-seeking young adults that may not benefit from psychotherapy techniques and are often concerned about the possible unpleasant side-effects of psychotropic medications. Also, the use of conventional anti-psychotics before formulating the diagnosis of a clear-cut psychotic disorder raises concerns about the potential risk of accelerating disease progression [58], as well as implications from forensic and ethical standpoints [59,60].

Second, the trial will be pursued with minimal risks for study participants, being PEA a well-established Food for Special Medical Purposes (FSMP) for prolonged therapy in several clinical conditions [52], nearly devoid of known or potential adverse effects [61]. Oral PEA has shown well-documented safety and tolerability in numerous clinical trials with over 1000 individuals with doses 300–1200 mg per day both in healthy and sick populations [53,54], with negligible acute and repeat dose toxicity [62]. Also, no invasive techniques will be implemented throughout the study.

Third, the feasibility of this proof-of-concept trial will justify its continuation as a larger Phase-3 study investigating PEA efficacy, tolerability, and acceptance in CHR subjects.

To this extent, randomization and blinding of future studies will be needed to help reduce possible biases. Also, being a single-site study, selected CHR individuals may differ to some extent from the population treated in normal life, making it difficult to interpret and generalize the results. Indeed, in line with the evidence that around 50% mental health disturbances start by late adolescence [4], when patients are referred to transition-age youth psychiatry services [63], future studies would probably benefit from the inclusion of underage participants (e.g., aged 15–18 years). Moreover, although CHR youths with APS are those most referred to mental health outpatient services [64], future studies should also consider including patients from the CHR-vulnerability group and the CHR-brief limited intermittent psychotic symptoms (BLIPS) group [1]. This approach could help capture potential variations in clinical responses across the CHR spectrum. Finally, more stringent systems for monitoring patient compliance with therapy (e.g., medication diaries, text messaging [65]) would enable more rigorous tracking of medication adherence by participants in future trials.

Net of the above considerations, an open-label single-arm design appears suitable for an early-phase trial in this specific clinical population [66] and may represent the initial ground to build a greater understanding of the possible correlations between behavior and biomarkers modulation as a response to PEA supplementation in CHR individuals.

## Figures and Tables

**Table 1 brainsci-14-01230-t001:** Study flowchart.

Procedures	Screening Phase	Feasibility Phase			Extension Phase	
	Screening (Day-7)	Baseline (Day 0)	T1 (4 weeks ± 7 Days)	T2 (12 Weeks ± 14 Days)	T3 (24 Weeks ± 14 Days)	T4 (36 Weeks ± 14 Days)
Informed consent	X					
Medical history	X					
Physical examination	X	X		X		X
Electrocardiogram	X	X		X		X
Urinalysis	X			X		X
*AUDIT* [37], *FTND* [38], *SDS* [39], *CEQ* [40]	X					
*TFLB* [41]		X	X	X	X	
Pregnancy test	X	X	X	X	X	
Hematology, biochemistry	X			X		X
Concomitant medication	X	X	X	X	X	X
Exclusion criteria	X	X				
Intelligence quotient	X					
*UKU-SERS* [42]		X	X	X	X	X
*Um-PEA* dispensing		X	X	X	X	
Compliance assessment			X	X	X	X
*CAARMS* [1]	X	X	X	X	X	X
*HADS* [43], *GF* Social/Role scales [44]		X	X	X	X	X
Microbiome, inflammation, eCBome blood and stool assessments		X	X	X	X	X

*AUDIT*, Alcohol Use Disorders Identification Test; *FTND*, The Fagerstorm Test for Nicotine Dependence; *SDS*, Severity of Dependence Scale; *CEQ*, Cannabis Experience Questionnaire; *TFLB*, The Timeline Followback; *UKU-SERS*, UKU Side Effect Rating Scale; *Um-PEA*, Ultramicronized-Palmitoylethanolamide; *CAARMS*, The Comprehensive Assessment of At-Risk Mental State; *HADS*, Hospital Anxiety and Depression Scale; *GF*, Global Functioning.

## Data Availability

The trial has been registered at Clinicaltrials.gov with identification code NCT06037993 (accessed on 5 December 2024). The patient information sheet and consent form are openly available at https://osf.io/nrc5b (accessed on 5 December 2024). The study case report form is openly available at https://osf.io/2vayh (accessed on 5 December 2024).
